### Orthodontic treatment and superstructure

Postoperative checkups will be completed after one, two, six and twelve weeks respectively. The patients will be instructed to rinse with a chlorhexidine digluconate solution in the first ten days postoperatively.

An impression will be taken of the implant with alginate and preformed caps and a model fabricated. A custom-designed palatal superstructure will be fabricated on the working model depending on malocclusion type and biomechanics requirements (Fig. 2).

**Figure 2 F2:**
[figure not shown]
Intraoral photograph of the upper jaw showing indirect implant anchorage (rigid connection between the anchorage teeth and implant) using a modified transpalatal arch.

Active orthodontic treatment starts for group 1 (implant loading after 12 post-surgical weeks) when the osseointegration period is completed and the implant shows good secondary stability. Active orthodontic treatment for group 2 (early implant loading) starts within 1 week after implant insertion, when the implant shows a good primary stability and ends after completion of active treatment.

### Outcome measurements

#### Primary Clinical Endpoints

Implants' stability after a loading time of 6 and 12 months of function after implant placement. The criteria of implant success are:

- implant survival

- no abnormal mobility

Implant stability will be tested post implant placement and throughout the orthodontic controls using the percussion test. Therefore the palatal implant in each case will be tapped then in vertical and horizontal directions using an instrument grip to test the subsequent resonance on percussion. High acustic sound response will indicate good primary and secondary implants' stability respectively, whereas dull acustic sounds will indicate loss of implants' stability.

In addition, resonance frequency analysis (RFA, Osstell™ mentor) will be used at time of surgery and at different times during postoperative checkups and finally after completion of active treatment. Resonance frequency analysis, firstly introduced by Meredith [13], is a method for clinically monitoring the implant stability in implant stability quotient (ISQ) units, which is scaled from 1 to 100. For measuring implant stability the orthodontic suprastructures will be removed.

#### Secondary Clinical Endpoints

Secondary clinical endpoints will include achievement of partial orthodontic treatment success 12 months after implant insertion, quantity of direct implant-bone interface of the removed bone specimens, patient's acceptance rate of palatal implants, anchorage loss of the anchor tooth unit and overall success after completion of active treatment.

Therefore, the set of model casts before and after 12 months' treatment will be compared in order to evaluate the partial orthodontic treatment success based on the peer assessment rating (PAR) index. The PAR index is an occlusal index, especially designed and validated as an objective instrument to measure how much the dentition of a patient deviates from normal occlusion. The index scores maxillary and mandibular alignment (crowding and spacing), buccal segment occlusion (anterioposterior, transverse and vertical), overjet (including anterior crossbite), overbite, and midline discrepancies. The more points the more severe is the malocclusion. Additional measurements such as the percentage of space closure in extraction cases, or the percentage of molar distalization will be taken.

The entire set of model casts before and after treatment will also be compared in order to evaluate the overall anchorage loss of the anchor unit, linear changes in the transverse dimension and finally to evaluate the overall treatment success, using the peer assessment rating (PAR) index. Analysis and superimposition of pretreatment and postreatment lateral cephalograms using Pancherz's analysis [14] will be performed to evaluate dental and skeletal changes by linear and angular measurements.

The objectives of the histomorphometric investigation will be to analyse quantitatively the percentage of direct bone-to-implant contact of the explanted orthodontic anchorage implants as well as to measure the distance between marginal bone surface and transmucosal implant neck of the explanted palatal implants in group 1 (implant loading after 12 post-surgical weeks) and group 2 (early implant loading within 1 week post surgery).

To investigate the removed bone specimens histomorphometrically, they will be immersed by ascending concentrations up to absolute ethanole for 2 weeks and will then be embedded in a mixture of glycol methacrylate (Technovit 7200 VLC^®^, Kulzer& Co Ltd., Wehrheim, Germany). Polymerisation will be obtained by light curing with a 450 nm wave length light source. From each specimen, sections parallel to the implant's longitudinal axis will be cut using a diamond band saw followed by grinding and polishing on an EXACT Microgrinding System (EXACT, Norderstedt, Germany) to a final thickness of 20 μm. The sections will be stained by toluidine-blue for transmission light microscopy.

In order to evaluate the patient's satisfaction and tolerance towards an implant-based orthodontic treatment, a questionnaire will be given to all patients at the end of active treatment, irrespective of malocclusion type and biomechanics.

The questionnaire will address the physiological and psychological responses of patients with special regard patient's comfort during an implant-based orthodontic treatment.

#### Tertiary Clinical Endpoints

As a tertiary endpoint, a histological and microtomography evaluation of all retrieved implants (about 2–3 years after placement) will be performed to obtain data on the performance of the SLA surface in human bone (Fig. 3a–c and 4a–c).

**Figure 3 F3:**
[figure not shown]
Histological evaluation of SLA^®^-surface performance in human bone. Specimens obtained due to the planned retrieval of Ortho^®^-implants at the end of orthodontic treatment. Bone-to-implant contact in the threaded body (a) and the neck region (b) of explanted human Ortho^®^-implants (Toluidine, original magnification 200 ×). (c) Immediate bone-to-implant contact along the SLA^®^-surface (Toluidine, original magnification 400 ×).

**Figure 4 F4:**
[figure not shown]
3 D Visualization with Micro-Computed Tomography (Institute of Applied Structure- and Microanalysis (ASMA), University of Mainz). Section of high-resolution micro-computed tomography scan for a retrieved conventional dental titanium implant (a-c). Internal structures are reconstructed as a set of flat cross sections, which were used to analyse the three dimensional morphological parameters of the implant with bone contact zones (a). Blue indicates bone architecture, red shows areas of direct bone-to-implant contact, while green indicates areas of no implant-bone interface (b-c).

In addition, a comparison between histomorphometric and microtomographic analyses will be performed on each specimen to evaluate the possibility of microtomography and to calibrate the technology for implant osseointegration assessment.

Moreover, the measurement reliability of the resonance frequency measuring device (Osstell™ mentor) in the assessment of implant stability will be evaluated by comparison between ISQ (implant stability quotient) values and the quantity of direct implant-bone interface of all retrieved implants.

Finally, the comparison between histomorphometric and resonance frequency analyses will also be used to define a standardized range of ISQ (implant stability quotient) readings for successful implant osseointegration for palatal implants.

### Statistical analysis

The entry, evaluation, and statistical analysis of all data and measurements are calculated using SPSS^® ^(Statistical Package for Social Science) software for Windows (Chicago, II, USA). Inter alia, the set of data will be analyzed based on implant survival rates.

An interim analysis will be performed for 62 palatal implants 6 months post-surgery. If the results of the interim analysis are an implant failure rate of more than 50 % in any group, the study will be terminated before the planned completion date.

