### Sample Size

For sample size calculation an implant failure rate of 5 % for group 1 (implant loading after a post-surgical healing period of 12 weeks) an implant failure rate of 25 % for group 2 (early implant loading within 1 week post implantation) was assumed. Based on 0.8 power to detect a significant difference at the two sided 5% level with an assumed loss to follow-up of 5 %, 62 patients in each group and 124 in total will be required. Sample size calculation, which based on clinical experiences with the new Orthosystem type II and early functional loading of conventional dental implants, was estimated with nQuery Advisor^® ^(Version 3.0) by the Institute of Medical Biostatistics, Epidemiology and Informatics (WH), University of Berlin, Germany.

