### Randomization

At each center, investigators and participants will be kept from knowing which patient will be assigned to which treatment group until post implant insertion. When according to the surgeon intraoperatively implant primary stability is given, participants will be randomly assigned either to the control or experimental group. Randomization will be performed in a 1:1 ratio using a balanced design with a block of 4 to treatment based on a computer-generated randomization code by an Institute of Medical Biostatistics (KKS, Mainz, Germany).

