### Timeframe of the study

The overall timeframe for the study is estimated to 5 years (12/2006-12/2011). Patient recruitment period will last 3 years.

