## Discussion

Clinical investigations and experimental studies indicate that endosseous implants e.g. palatal implants are resistant to orthodontic force application and can be used to achieve positional stability and therefore to enhance orthodontic anchorage [1,2,4,5,8,11]. Usually, according to the present manufacturers' instructions and to conventional loading concepts in general dental implantology, the healing period for palatal implants must not fall short of 3 to 4 months.

Recent findings from clinical and experimental studies suggested the possibility of loading palatal implants earlier than 12 weeks. Borbély and coworkers [8] showed, that an sufficient amount of osseointegration could be achieved at about 4 weeks after surgery or even at an earlier time. This result was based on clinical and histological evaluation in an experimental animal study (foxhounds). Study endpoints were defined as implant loss and implant stability after 1 and 6 months of loading.

Crismani and coworkers [11] initiated a clinical pilot study to evaluate the behaviour of 20 early loaded palatal implants over an observation time of 12 weeks. They reported a success rate of 90% for implants functionally loaded after a healing period of 1 week. The implants, however, were observed no longer than for the 12 week period.

Therefore, we initiated an RCT study comparing and contrasting the effect of early loading of palatal implant therapy versus implant loading after 12 weeks post implantation using the new ortho-implant type II anchor system device (Orthosystem Straumann, Basel, Switzerland). The results of this trial will be presented as soon as they become available.

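### The one stopping look stated in the article comes when about two thirds of patients are randomised, so it can limit exposure to early loading only for about the last third

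*Protocol article*

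**What the plan says.** All references are to the protocol article.

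- **Statistical analysis** fixes the timing: "An interim analysis will be performed for 62 palatal implants 6 months post-surgery". It attaches one consequence: with an "implant failure rate of more than 50 % in any group, the study will be terminated before the planned completion date".
- **Sample Size** sets the total: "62 patients in each group and 124 in total will be required". It assumes 5% failure in group 1 and 25% in group 2.
- **Timeframe of the study**: "Patient recruitment period will last 3 years". No recruitment pause is stated while the 62 interim implants reach 6 months.
- **Randomization**: "Randomization will be performed in a 1:1 ratio using a balanced design with a block of 4".
- **Orthodontic treatment and superstructure**: "Postoperative checkups will be completed after one, two, six and twelve weeks respectively". The same part of the article has group 2 loaded within 1 week of insertion and group 1 after 12 weeks.
- **Outcome measurements** has stability tested by percussion from placement onwards, with resonance frequency readings at surgery and during the postoperative checkups.
- **Discussion**, on an earlier pilot of 20 early-loaded palatal implants: "They reported a success rate of 90% for implants functionally loaded after a healing period of 1 week". It adds that observation ended at 12 weeks.

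**The concern.** Whether early loading is clinically safe is the first question under Study objectives, and the only consequence tied to the interim analysis is a stop for failures. Such a rule protects patients who have not yet been exposed. In group 2 exposure begins within a week of insertion, so the share already randomised at the look is close to the share beyond the rule's reach.

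The trigger requires half the sample to be followed for 6 months while recruitment continues. If early loading failed very often in the first weeks, the checkups would record it, but no stopping rule stated in the article would use those data until the second half of recruitment was well under way.

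**Working it through.** **Inputs.** Total 124, recruitment 36 months, trigger 62 implants at 6 months, 1:1 allocation in blocks of 4, limit above 50% in a group. Even accrual is an assumption, because the article gives no accrual curve.

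**The plan's sample size.** Two proportions, 5% versus 25%, two-sided 5%, power 80%, with continuity correction: 59 per group. Allowing for 5% loss, 59 × 1.05 = 62 (59/0.95 gives 63). The 62 per group is reproduced, so 124 is a sound base.

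**Time of the stated look.**
- Accrual: 124/36 = 3.44 per month.
- 62nd implant: 62/3.44 = month 18; 6 months later is month 24.
- Enrolled at month 24: 24 × 3.44 = 82.7, which is 66.7% of 124. Still to come: 41.3.
- Enrolled during the 6-month wait alone: 6 × 3.44 = 20.7.
- In group 2 by month 24: 82.7/2 = 41.3. Less than one patient enters per week, so almost all of these are already loaded.
- In group 1, about 9.5 patients enter in any 12 weeks, so about 5 are still in their healing period.

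**Sensitivity.** N(t) = 124(t/T)^k, with T the recruitment length in months.

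| Assumption | Enrolled at the look |
|---|---|
| T = 36, k = 0.75 (mildly front-loaded) | 65% |
| T = 36, k = 1 (even) | 67% |
| T = 36, k = 1.5 | 71% |
| T = 36, k = 2 (slow start) | 76% |
| T = 36, even, 62 evaluable after 5% loss | 69% |
| T = 36, even, 3-month data lag | 75% |
| T = 24, even | 75% |
| T = 48, even | 62.5% |

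A strongly front-loaded curve, N = 124(1 − (1 − t/36)²), gives 71%. With a 3-month data lag the T = 36 power curves run from 72% to 92%.

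**Time of an earlier look at 12 weeks (2.8 months).**
- First 31 implants: 31/3.44 = 9.0; 9.0 + 2.8 = month 11.8; 11.8 × 3.44 = about 41 enrolled (33%).
- First 62 implants: 18.0 + 2.8 = month 20.8; about 72 enrolled (58%). Against 67% at the stated look, this gains about 11 patients, 5 or 6 of them in group 2.

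Only the 31-implant look changes exposure much: about 83 − 41 = 42 fewer patients randomised, about 21 of them to early loading.

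**How the stated limit behaves at that look.** Seven complete blocks of 4 give 14 group 2 implants among 28. The next three patients add 1 or 2, making 15 or 16. More than 50% means at least 8 of 15 or at least 9 of 16. Binomial tail probabilities:

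| True 12-week failure in group 2 | 8+ of 15 | 9+ of 16 |
|---|---|---|
| 25% | 1.7% | 0.7% |
| 60% | 79% | 72% |
| 70% | 95% | 93% |

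For comparison, the stated look with 31 per group needs at least 16 failures; at 25% failure its chance of stopping is 0.13%.

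**The case against.** The stated timing is defensible. One look at half the sample is conventional, and 6 months matches the first time point in the primary endpoint. The section contains no contradiction or wrong figure. Four further objections limit the point.

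- **The pilot.** A reader might infer from it that most early-loading failures happen before 6 months. It cannot show that: follow-up ended at 12 weeks, and 90% success in 20 implants means 2 failures (exact 95% interval about 1% to 32%). Set beside the assumed 25%, the pilot's 10% would leave room for many later failures. It shows only that early failures occur. This is a reason to keep the 6-month look.
- **The comparison at 12 weeks.** Group 1 is not yet loaded, so a between-group excess at that time would set loaded against unloaded implants. This objection stands. The limit is stated per group, however, so group 2 can be judged alone.
- **The effect at the planned rates.** A reader might take 25% of the 41 early-loading patients, about 10 failures, as avoidable harm. The documents do not support this. At a true rate of 25% the 50% limit is almost never crossed, whenever the look is held.
- **Other safeguards.** It would go too far to say that nothing could be done before month 24. A coordination centre monitors progress, patients are examined repeatedly, and ad hoc safety review may be described in the full protocol. What stands is that no other stopping rule is stated in the article.

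**Conclusion.** The point holds in a limited form. Under even accrual over 36 months, the only stated stopping look falls near month 24 with about 67% of patients randomised and nearly all enrolled group 2 patients loaded. The figure is about 65% to 76% for other accrual shapes over 36 months, 62.5% if recruitment took 48 months, and higher with any data lag. The rule can therefore limit exposure only for about the last third.

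An earlier look matters only if early failure is very high, which is the situation the 50% limit is written for. At the planned 25% it would change almost nothing. The conclusion assumes no recruitment pause and no earlier rule in the full protocol; the article states neither.

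**What to change.** Keep the 6-month look on 62 implants. Add one harm-only look when the first 31 implants have 12-week data, near month 12 under even accrual. At that look:

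- judge group 2 on its own against the limit the protocol already states, because group 1 is not yet loaded;
- count every implant lost or mobile since insertion;
- report the actual number of group 2 implants, since it may differ from 15 or 16 if blocks are run separately by centre.

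A second early look, at 12 weeks in the first 62 implants, is not worth adding.

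The cost is a protocol amendment and one short tabulation from checkups already scheduled. A look that can stop only for harm gives no added opportunity to claim benefit falsely. The price is a chance of about 0.7% to 1.7% of stopping at this look if the true 12-week failure rate in group 2 is 25%, and less if it is lower.

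### The only stated interim rule, more than 50% failures in any one group, compares no groups and would rarely act until early-loading failure approaches one half

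*Protocol article*

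**What the plan says.** The Statistical analysis section of the protocol article sets the interim look: "An interim analysis will be performed for 62 palatal implants 6 months post-surgery". The only action attached to it is that, given "an implant failure rate of more than 50 % in any group, the study will be terminated" before its planned end. The section gives no between-group criterion and no reason for choosing 50%.

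The Sample Size section supplies the planning rates: "an implant failure rate of 5 % for group 1" (loading after 12 weeks) and "an implant failure rate of 25 % for group 2" (early loading). It continues: "Based on 0.8 power to detect a significant difference at the two sided 5% level", and concludes that "62 patients in each group and 124 in total will be required".

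Under Study objectives, the question is whether early loading is clinically safe, and the null hypothesis is that the two groups have the same implant failure rate. The objective is therefore comparative. Randomization is 1:1 in blocks of 4, and recruitment is planned to last 3 years.

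**The concern.** An interim rule that stops a trial because of failures serves the patients not yet randomised. Here the threshold is an absolute rate in a single group, set at twice the early-loading planning rate (50/25) and ten times the control planning rate (50/5). Because the rule does not compare groups, a very large excess of failures under early loading over a control group with almost none has no effect on it until more than half of the early-loaded implants have failed.

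At stake is exposure during the trial: the rule could stay silent on strong evidence of harm while patients continue to be assigned to early loading. The final test and its error rate are not at stake.

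**Working it through.** **Inputs.** From Sample Size: failure rates of 5% and 25%, power 0.80, two-sided 5% level, 5% loss to follow-up, 62 per group. From Statistical analysis: 62 implants at the interim look, limit above 50% in any group. From Randomization: 1:1 allocation. From Timeframe of the study: 3 years of recruitment. The interim split of 31 per group is an assumption drawn from 62 implants at 1:1.

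**Step 1: the plan's own sample size.**

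n = [1.96·√(2·0.15·0.85) + 0.8416·√(0.05·0.95 + 0.25·0.75)]² / 0.20² = (0.990 + 0.408)² / 0.04 = 48.8

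With continuity correction: n = (48.84/4)·[1 + √(1 + 4/(48.84·0.20))]² = 58.4, so 59 per group. Allowing for 5% loss, 59 × 1.05 = 61.95, so 62; or 59/0.95 = 62.1, so 63. The stated 62 is reproduced, and the sample size is not in question.

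**Step 2: what the rule requires.** More than 50% of 31 means at least 16 failures in one group. The largest early-loading count that does not trigger it is 15/31 (48.4%).

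**Step 3: how often it triggers.** P(trigger) = P(X ≥ 16), with X binomial (31, p):

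| True early-loading failure rate p | P(trigger) |
|---|---|
| 25% (planning rate) | 0.13% |
| 30% | 0.95% |
| 40% | 12.8% |
| 45% | 28.7% |
| 50% | 50% |
| 60% | 87% |

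The exact split matters little. With 30 or 32 implants in the group, the figures are 0.08% or 0.06% at 25%, and 9.7% or 9.2% at 40%.

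**Step 4: results that would not trigger it.** Two-sided Fisher exact test, 31 per group:

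| Early loading | Control | p |
|---|---|---|
| 15/31 | 0/31 | 0.000006 |
| 15/31 | 1/31 | 0.00007 |
| 15/31 | 2/31 | 0.0004 |
| 15/31 | 3/31 | 0.0016 |
| 13/31 | 1/31 | 0.0005 |

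**Step 5: patients still to come.** With uniform accrual, 124/36 = 3.44 patients enter per month. The 62nd enters at month 18, so the look falls at month 24, when 24 × 3.44 ≈ 83 are enrolled. That leaves 124 − 83 = 41, of whom about 20 would go to early loading.

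**Step 6: a comparative benchmark.** Take a boundary at two-sided Fisher p ≤ 0.001 in the direction of excess early-loading failure. With 0, 1 or 2 control failures of 31 it is crossed at 10, 13 or 14 early-loading failures. Its stopping probability is the sum of the products of the two binomial probabilities over all pairs of counts that cross it, with the control rate at 5%:

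| True early-loading rate | Comparative boundary | Stated rule |
|---|---|---|
| 5% | below 0.0001% | practically 0 |
| 10% | about 0.01% | practically 0 |
| 25% | 6% | 0.1% |
| 40% | 44% | 13% |
| 45% | 62% | 29% |
| 50% | 77% | 50% |

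**The case against.** **A lenient limit is not an inconsistent one.** The planning rates serve the power of the final test, while the interim limit is an emergency stop. A limit above the assumed rate does not conflict with that rate, and a limit near 25% would often end the trial under the very scenario it was sized to study. This stands: a reader might infer that the 50% limit contradicts the sample-size assumptions, and it does not.

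**The control group is covered.** The rule applies to any group, so failures above 50% in the control group would also stop the trial. It would be wrong to infer that the rule ignores the control group. What it lacks is a comparison with it.

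**The extreme results are unlikely at the planning rates.** At 25%, 15 or more failures of 31 occur with probability 0.4%. The expected interim picture is about 8/31 against 1/31 or 2/31 (Fisher p = 0.026 or 0.081), and continuing on that is defensible. This also stands. The weakness lies at true rates well above 25%, such as 40%, where the rule stays silent 87% of the time. The strict benchmark is itself modest at 25%, where it stops only 6% of the time.

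**Other oversight may exist.** The article condenses a fuller protocol that is not shown, and it mentions ethics approval and a coordination centre monitoring progress. A reader might infer that the trial would run on through overwhelming harm. The article supports only the narrower statement that this rule would not trigger.

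**A comparative boundary has complications.** At 6 months after surgery the early group has been loaded for about 6 months and the control group for about 3, which could tilt a comparison towards harm. A harm stop is also an extra route to rejecting the two-sided null hypothesis. Both points favour a strict boundary and a note on how to read it. They do not support having no comparison at all.

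**Conclusion.** The point holds as a weakness in a stated rule; it is not an arithmetical error or an internal contradiction. With about 31 implants per group the rule needs 16 failures in one group. It triggers with probability 0.1% at a true early-loading failure rate of 25%, 13% at 40% and 50% at 50%, and a result of 15/31 against 1/31 does not trigger it. For a trial whose safety question is comparative, that is little protection for the patients still to be randomised.

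The conclusion rests on three assumptions: an even interim split (30 or 32 in a group changes little), uniform accrual for the figure of 41, and rates read as the probability of failure by the 6-month look. The Sample Size section gives no time point for its rates. If fewer failures have occurred by 6 months than by the end, the rule triggers less often still.

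A reader might rank this as an error that undermines the trial. The documents do not support that: the primary comparison and its error rate are untouched, and other oversight cannot be excluded. It should be fixed, as a cheap improvement in patient protection.

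**What to change.** At the look already planned, add a between-group harm boundary in the direction of excess early-loading failure. State its operating characteristics, let the sponsor and ethics committee choose the level, and give the reason for the 50% limit if it is kept alongside. The Statistical analysis section should then be reconciled with the comparative hypothesis under Study objectives and the rates under Sample Size.

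A Haybittle-Peto-type limit of two-sided Fisher p ≤ 0.001 is one illustration, with the performance shown in the working. Because the level is so strict, it adds at most 0.001 to the chance of falsely rejecting the null hypothesis, so the two-sided 5% final test is left essentially intact.

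The cost is one paragraph, with no extra look and no extra data. The downsides are a very small chance of stopping when early loading is only slightly worse (about 0.01% at 5% versus 10%) and the unequal loading time at 6 months, which the text should mention as a caution when the boundary is read.
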